# The efficacy and safety of *Danggui-Sayuk-Ga-Osuyu-Saenggang-tang* on Korean patients with cold hypersensitivity in the hands: study protocol for a pilot, double-blind, randomized, placebo-controlled, parallel-group clinical trial

**DOI:** 10.1186/s13063-017-2002-8

**Published:** 2017-06-08

**Keywords:** Herbal medicine, Cold temperature, Cold hypersensitivity, Randomized clinical trial

## Abstract

**Background:**

In recent years, cold hypersensitivity in the hands (CHH) has become a common ailment of women in Korea. It can lead to gynecological problems such as irregular menstruation, miscarriage, and infertility. Traditionally, Korean herbal medicine has been the primary treatment method used to balance thermoregulation in the human body; however, its effectiveness has not been confirmed through systematic study. Thus, in this trial, we will investigate the feasibility of a full randomized clinical trial, *Danggui-Sayuk-Ga-Osuyu-Saenggang-tang* (DSGOST) in Korean women with CHH.

**Methods:**

This study will be a pilot, multicenter, double-blind, randomized, parallel-group, two-arm, placebo-controlled clinical trial. A total of 66 participants will be randomly divided into two groups, a DSGOST treatment group and a placebo control group, in a 1:1 ratio using a web-based randomization system. Each group will take DSGOST or placebo three times daily for 6 weeks. The primary outcome will be measured using Visual Analogue Scale (VAS) scores of CHH. Secondary outcomes will include changes in skin temperature of the hands, Clinical Global Impressions (CGI) scale scores, recovery rate of skin temperature of the hands after the cold stress test, and the Korean version of the WHO Quality of Life Scale, abbreviated version (WHOQOL-BREF).

**Discussion:**

This trial will be the first trial to reflect the newly defined disease range of CHH which was compiled by Korean medicine expert consensus. This study will provide considerable evidence for further large-scale trials and general clinical guidelines for CHH in the Korean medical field.

**Trial registration:**

This study is registered at ClinicalTrials.gov, ID: NCT02645916. Registered on 30 December 2015.

**Electronic supplementary material:**

The online version of this article (doi:10.1186/s13063-017-2002-8) contains supplementary material, which is available to authorized users.

## Background

Cold hypersensitivity in the hands (CHH) is a condition where the individual feels colder in the upper extremities than colder other people in any environment [1, 2]. CHH is not a fatal disease, but can worsen quality of life by interfering with daily activities. According to a Korean genetic etiology and phenotype of CHH study, there are more female CHH sufferers than males with an approximate prevalence ratio of 3:2 [3]. Through reviewing previous CHH-related studies, we found out that studies based on the Asian population were more frequently performed than in the western population. Among the studies, Li et al. reported that the prevalence rates of women with CHH by country are 54.3% in Japan, 25% in Korea, and 20% in China [4].

In conventional medicine, CHH is the representative clinical symptom of Raynaud’s phenomenon (RP) which is classified in the *International Classification of Diseases, 9th edition* (ICD-9) as a peripheral vascular disease. It is thought that an increase in α_2_ sympathetic receptor activity causes the vasoconstriction of blood vessels and central thermoregulatory dysfunction in CHH, but its pathophysiological mechanism is not completely clear [5]. Due to the uncertain pathology and nonstandardized diagnostic and treatment methods of CHH, most conventional physicians prefer to identify CHH by the occurrence of symptoms during the cold stimulation test which is one of the primary diagnostic tests for RP [6]. The general treatment of RP is similar to the allopathic treatments of RP, including vitamin E, calcium-channel blockers, and lifestyle modification, but the efficacy of such treatments is controversial [7].

In Korea, treating CHH with traditional Korean herbal medicine is often preferred to conventional medicine. Because Korean medicine takes a holistic approach to the ailment, it is considered to be a cold-related symptom and is also classified as cold syndrome pattern. Balancing *yin* and *yang* energy in the body with holistic and personalized therapy is one of the advantages of Korean medicine which is more acceptable in Korean society other than symptom-based treatments.

Based on traditional medicine theory, women’s disease is generally caused by cold pathogenic factors [8] which can easily lead to cold-related syndromes such as CHH. Many people consider CHH to be a mild symptom, but it should be treated with careful attention before it worsens and leads to more severe problems.

*Danggui-Sayuk-Ga-Osuyu-Saenggang-tang* (DSGOST) is the one representative traditional Korean herbal medicine formula used to treat CHH since ancient times [9]. The traditional Chinese medicine (TCM) classic, *Shanghanlun* mentions that DSGOST is the appropriate prescription for patients who have had pathogenic internal cold for a long time [10]. It is composed mainly of herbs that can disperse cold and tonify the blood in order to enhance the healing capacity of the body system from cold damage [11]. Nishida et al. [12] found that DSGOST treatment for 8 weeks helped to improve the severity of peripheral coldness and blood flow in female Japanese patients. In our research team, we also found that DSGOST relaxes both the endothelial and vascular smooth muscle cells by inhibiting cold-induced activation of the Ras homolog gene family member A (RhoA) and blocks the endothelin-1-mediated paracrine pathway for the cold response in blood vessels [13]. Although it has a long history of use for CHH, there has been no clinical trial performed to evaluate the potential efficacy of DSGOST in the Korean population. For that reason, through this multicenter, randomized, placebo-controlled trial with participant and investigator blinding, we will examine the feasibility of a full randomized clinical trial of DSGOST on Korean female patients with CHH in order to provide more convincing evidence for the treatment of CHH using herbal medicine.

## Methods

### Trial design

This trial is a pilot, multicenter, double-blind, randomized, parallel-group, two-arm, placebo-controlled clinical trial that will be conducted in the Department of Internal Medicine at Gachon University, Gil Oriental Medical Hospital, Dongguk University, Ilsan Oriental Hospital, Sangji University Oriental Medical Centre, Semyung University Second Affiliated Oriental Medical Hospital at Chungju, and the Department of Gynecology, Kyung Hee University Oriental Medical Center, Kyung Hee University Oriental Medicine Hospital at Gangdong in Korea.

We will recruit 66 participants in total. Once the participant decides to take part in this trial, there will be at least a 2-week run-in period prior to randomization. After randomization, each participant will be treated for 6 weeks and visit the clinic once every 2 weeks. The total trial duration will be 8 weeks. The flow chart of the trial is shown in Fig. 1.

**Fig. 1 Fig1:**
[figure not shown]
Flow chart of the trial process

### Randomization

Eligible participants who consent to participate will be randomly assigned to either the treatment (DSGOST) or the placebo group with an allocation ratio of 1:1. Assignment will be done with the web-based randomization system developed by the contract research organization (CRO), the Institute of Safety and Effectiveness Evaluation for Korean Medicine (ISEE). The random sequence will be generated by an independent professional statistician from the CRO using the SAS 6.1 program and stratified by hospital using random block sizes of 2 and 4.

### Blinding

Once the participant is randomly allocated to a group, neither the investigator nor the participant will know which type of the drug the participant receives until the end of the trial. The trial drugs will be manufactured in packages that are indistinguishable in appearance and then distributed by independent research pharmacists or assistants who are also blinded to the randomization, in each hospital. When voluntary withdrawals or urgent medical situations, such as severe adverse events (SAEs), are encountered, the principal researcher of the hospital will inform the sponsor and the CRO immediately to handle unblinding according to standard operating procedures (SOPs).

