### Recruitment

Participant recruitment will take place in six hospitals of Korean medicine in various Korean cities. Each institution will advertise the trial by posting recruitment posters on the hospital website or bulletin board. If necessary, the local community newspaper advertising will also be considered.

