### Adverse event reporting

All participants will be required to report any adverse events (AE) that occur during the trial at every visit. Each AE must be recorded in the CRF by the site investigator. All AEs will be assessed for causality. If serious adverse events (SAEs) occur, the Institutional Review Board (IRB) and principle investigator will be notified as soon as possible. After receiving an SAE report, the site investigator will decide whether the participant must withdraw or whether they may continue to participate in the trial.

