### Sample size calculation

This clinical trial is a pilot study to examine the feasibility of a full randomized clinical trial of DSGOST and determines the effect size for further large-scale studies. We required a sample size of 66 based on requiring data from 25 participants per arm to calculate estimates of treatment effect to inform the power calculation for a main study. We accounted for a 20% dropout rate based on a similar study [16].

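### Voluntary withdrawal is named beside medical urgency as an occasion for unblinding, which needlessly erodes the blind; the leak to other patients is a hint rather than a disclosure

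*Protocol article*

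**What the plan says.** The Blinding section of the protocol article promises that "neither the investigator nor the participant will know which type of the drug the participant receives until the end of the trial". The same paragraph then turns to unblinding and gives its occasions as follows: "When voluntary withdrawals or urgent medical situations, such as severe adverse events (SAEs), are encountered". The two kinds of event are joined by *or* and lead to the same action. On either of them, the lead researcher at the site has a single duty, namely that he or she "will inform the sponsor and the CRO immediately to handle unblinding according to standard operating procedures (SOPs"). The SOPs are not part of the article.

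The Withdrawals section lets a participant leave whenever she wishes and on whatever grounds. It asks only that the reason be recorded and the data analysed by intention to treat. It does not mention the code.

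The Randomization section assigns patients "with an allocation ratio of 1:1". It describes the list, which a CRO statistician draws up, as "stratified by hospital using random block sizes of 2 and 4". Under Recruitment there are six hospitals, and the total is 66 patients. The primary outcome is a patient-rated VAS. The CGI is rated by a physician, and the section on it acknowledges that the condition is subjective. All adverse events are assessed for causality.

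On terminology, the Blinding section and the abbreviation list expand SAE as *severe* adverse event. The Adverse event reporting section writes "If serious adverse events (SAEs) occur, the Institutional Review Board (IRB) and principle investigator will be notified".

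**The concern.** A medical urgency can create a need to know what the patient took. Leaving the study does not in itself create one, and the article offers no reason why it should. Read as written, the sentence opens a route to unblinding for a patient who has simply lost interest, in the same paragraph that promises a blind to the end.

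Three things are at stake if a code reaches the site:

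- Any judgement still to be made on that patient, such as adverse event causality, is no longer blind.
- Because allocation is blocked within small hospital strata, the opened code says something about patients enrolled next to her. Their CGI is rated by site physicians.
- If a neighbouring place is not yet filled, concealment of the next allocation is weakened.

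**Working it through.** **Inputs.** From the article: 66 patients, six hospitals, 1:1 allocation, random blocks of 2 and 4, 20% dropout. Assumed: 11 patients per hospital (66/6), and each block of size 2 or 4 with probability 1/2.

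**The plan's own figure.** The Sample size section states: "We required a sample size of 66 based on requiring data from 25 participants per arm". With 20% dropout, 25/(1 − 0.20) = 31.25, rounded up to 32 per arm, or 64 in total. This is within two of 66, and the present point does not touch it.

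**How many codes at most.** 0.20 × 66 = 13.2, or 0.20 × 11 = 2.2 per hospital. This is a ceiling for withdrawal-driven openings at the planned dropout rate. It requires every dropout to be a voluntary withdrawal and every such code to be opened.

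**One opened code, boundaries unknown.** All block sizes are even, so patients 1 and 2, 3 and 4, and so on always share a block. Let u(k) be the probability that a block starts at pair k. Then u(1) = 1, u(2) = 1/2, and u(k) = [u(k−1) + u(k−2)]/2, giving 1, 0.5, 0.75, 0.625, 0.6875 for the five pairs. The pair is a whole block of 2 with probability u(k)/2, and the mate is then certainly on the opposite arm. Otherwise it lies in a block of 4, and the mate is opposite with probability 2/3. Hence:

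P(mate opposite) = 2/3 + (1/3) × u(k)/2

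| Pair | 1 | 2 | 3 | 4 | 5 |
|---|---|---|---|---|---|
| P(mate opposite) | 0.833 | 0.750 | 0.792 | 0.771 | 0.781 |

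Patients in pairs k and k+1 share a block of 4 with probability u(k)/2, so P(opposite) = 1/2 + (1/6) × u(k)/2, which is 0.54 to 0.58. Patients further away stay at 0.50. A single code never gives certainty.

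**Several opened codes, boundaries unknown.** Exact enumeration of all sequences for a hospital of 11 gives:

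- two codes opened: mean best-guess accuracy for the others 58%, and 0.04 patients fully determined on average;
- three codes opened: 61% and 0.14 patients;
- each code opened independently with probability 0.20: 1.2% of remaining patients fully determined and a mean best guess of 58%. Over the trial 0.80 × 66 = 52.8 patients remain, so 0.012 × 52.8 ≈ 0.6 of a patient is determined.

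**Same openings, boundaries known.** One third of patients sit in blocks of 2 and two thirds in blocks of 4.

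- Block of 2: determined if the mate is opened, 0.20.
- Block of 4: determined if two of the other three are opened and both are on the opposite arm, or if all three are opened: 3 × 0.2² × 0.8 × 1/3 + 0.2³ = 0.032 + 0.008 = 0.040.
- Overall: 0.20/3 + 0.040 × 2/3 = 0.093, or 0.093 × 52.8 ≈ 4.9 patients.

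**After the change.** Withdrawals alone open no codes, and the best guess for any other patient stays at 50%.

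**The case against.** The strongest reply is that the sentence does not say every withdrawal is unblinded. It says that sponsor and CRO are told so that unblinding can be handled under SOPs. Those SOPs may call for a decision case by case, or may keep the code away from the site. Who receives a code is a detail that an article may leave to them. This stands, and it makes every count above an upper illustration. It does not explain why withdrawal appears in the sentence at all.

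A reader might infer that one opened code fixes the partner's allocation, or that some 9% of remaining patients are determined and 35% at least partly revealed (0.20/3 + 0.424 × 2/3 = 0.35, where 0.424 is the share in blocks of 4). Both readings need known block boundaries. The sizes vary at random, so publishing them does not reveal the boundaries.

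A reader might also infer damage to the primary outcome. That route is weak. A continuing patient would have to learn another patient's code and the enrolment order. A withdrawn patient's VAS values recorded before the code was opened cannot be altered by it, and those are what last observation carried forward uses. The physician-rated CGI and causality assessments are the more plausible routes.

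Finally, small blocks might look like the fault to correct. With about 11 patients per hospital and web-based allocation, varying blocks of 2 and 4 are a defensible choice for balance. Recruitment has been open since December 2015, so a new list would alter a running trial for little gain once withdrawal codes stay closed.

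**Conclusion.** The point holds as a fault in a stated rule. The Blinding section names voluntary withdrawal as an occasion for handling unblinding, against its own promise of a blind to the end, and neither it nor the Withdrawals section gives a need for the allocation.

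The size is modest. One code known at the site moves the best guess for the paired patient from 0.50 to between 0.75 and 0.83. At the ceiling of about 13 openings, about 1% of remaining patients are determined with boundaries unknown and about 9% with boundaries known. This rests on 11 patients per hospital, equally likely block sizes, every dropout being a voluntary withdrawal that is unblinded and disclosed to the site, and site staff knowing the enrolment order. The documents do not support the reading that 13 codes will in fact be opened.

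The difference between *severe* and *serious* is a genuine inconsistency of wording, but it is separate and adds nothing to the weight of this point.

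**What to change.** In the Blinding section, remove voluntary withdrawal as an occasion for unblinding, and state that the codes of patients who withdraw stay closed until database lock. Leave the urgent medical route as it stands. Bring the SOP into line, and let the Withdrawals section say the same so that the two sections agree. Make no change to the block sizes or the randomisation list.

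Separately, reconcile *severe* and *serious* for SAE across the Blinding section, the Adverse event reporting section and the abbreviation list.

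The cost is a wording change in the protocol and SOP, with whatever notice the six review boards require. Sample size, allocation and analysis are unaffected.

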## Participants

### Inclusion criteria

This study will enroll a total of 66 patients who have a complaint of CHH and who are eligible according to the following criteria:Female subjects aged 19 to 59 years who have a complaint of CHH.Patients must have at least one of the following symptoms:Symptoms of CHH at a temperature at which most individuals feel no coldSymptoms of extremely cold hands upon cold temperature exposureThose who, upon return to a warmer environment, continue to have symptoms of cold hands
A 4-cm or greater Visual Analog Scale (VAS) CHH scoreThose in whom the thermal difference between the palm (PC8) and the upper arm (LU4) is higher than 0.3 °CThe ability to comply with all study-related procedures, medications, and evaluationsThe signing of a written Informed Consent Form

### Exclusion criteria

The exclusion criteria are as follows:Patients who have taken calcium antagonists or beta-blockers for the purpose of treating CHHThose who have gangrene or ulceration on one or more fingersThose who have been diagnosed with hypothyroidism or are currently taking thyroid medicationsThose who have been diagnosed with an autoimmune disease or have a positive antinuclear antibody (ANA) test resultThose who have been diagnosed with carpal tunnel syndrome or have positive Tinel’s and Phalen’s testsThose who have been diagnosed with cervical disc herniation or have a malignant tumorThose who have been diagnosed with diabetesThose who are currently medicated with drugs that may affect CHH symptoms such as anticoagulantsThose who have a moderate level of liver dysfunction (each of AST and ALT greater than 100 IU/L) or kidney dysfunction (creatinine greater than 2.0 mg/dL)Those who currently receive psychological or psychiatric treatment due to any mental illness, such as behavior disorder, depression, anxiety, neurosis, schizophrenia, or any other serious mental illnessThose who have been diagnosed with moderate anemia or hematological disorders (adult nonpregnant women hemoglobin (Hgb) level less than 7 g/dL, hematocrit (Hct) less than 26%, white blood cell (WBC) level greater than 11,000/mm^3^)Those whose systolic blood pressure (SBP) is greater than 180 mmHg or whose diastolic blood pressure (DBP) is greater than 100 mmHg, based on the average of at least two measurementsThose with an arrhythmia that shows on an electrocardiogram (ECG) or who have been diagnosed with heart diseases such as ischemic heart diseaseThose who are addicted to alcohol or drugsThose who are pregnant (positive urine-HCG) or lactating or may become pregnantThose who are currently participating in other clinical trialsThose who are unable to understand and speak KoreanThose who are judged to be inappropriate for the clinical study by the researchers such as refusal to comply, forgetting visits, lack of comprehension, etc.

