### Interventions

After enrollment, participants will take 9 g of DSGOST or placebo drug per day, for 6 weeks. Both groups will take the assigned drugs orally with warm water three times a day, at least 30 min after a meal.

The investigational drug, DSGOST is a well-known traditional herbal formula for treating cold syndrome in traditional medicine. In this trial, we will use DSGOST granulated extract (manufactured by Hanpoong Pharm and Foods Co., Ltd. (HP)) for convenience of use. It contains 1.33 g of *Zingiberis Rhizoma*, 1.67 g of *Zizyphi Jujubae Fructus*, 1.00 g of *Cinnamomi Ramulus*, 1.00 g of *Paeoniae Lactiflorae Radix*, 1.00 g of *Angelicae Gigantis Radix*, 0.67 g of *Asari Radix*, 0.33 g of *Evokiae Fructus*, 1.00 g of *Akebiae Lingnum*, and 0.67 g of *Glycyrrhizae Radix*.

Placebo drug will also be prepared and will pass several quality assurance tests. It will have a relatively similar color, shape, weight, odor, and taste to DSGOST so that participants will not notice whether they are given the real drug or placebo. The daily dose of placebo granules contain 5.1 g of lactose, 3.0 g of cornstarch, 0.3 g of citric acid, 0.3 g of pigments, and 0.3 g of *Ssanghwa* herbal flavor.

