### Safety assessment

The safety assessment, including physical examination, renal function tests (blood urea nitrogen (BUN), creatinine), and liver function tests (ALT, AST, and γ-GT), will be conducted at visits 2 and 5. Vital signs will be checked at every visit.

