### Ethical consideration

This trial was approved by the Institutional Review Board (IRB) of six different hospitals (Gachon University Gil Oriental Medical Hospital: 15-103, Kyung Hee University Oriental Medical Center: KOMCIRB-150818-HR-032, Kyung Hee University Oriental Medicine Hospital at Gangdong: KHNMCOH2015-09-002-002, Dongguk University Ilsan Oriental Hospital: 2015-09, Sangji University Oriental Medical Centre: SJIRB-DRUG-15-002, and Semyung University Second Affiliated Oriental Medical Hospital at Chungju: 1511-08). This study will abide by the amended Declaration of Helsinki and the regulations of the “Good Clinical Practice” principles of the Korea Food and Drug Administration (KFDA). The current protocol version is 1.5 and it has been developed according to the Standard Protocol Items: Recommendations for Interventional Trials (SPIRIT) Statement (see Additional file 1). All items from the World Health Organization Trial Registration Data Set have been drawn. All participants will receive sufficient explanation and time to determine trial participation. Written informed consent will be obtained from all participants before beginning any trial procedures.

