## Discussion

CHH is a subjective symptom that is commonly seen in women in Korea. In conventional medicine (CM), CHH is categorized as an associated symptom of vascular diseases such as RP and hand-arm vibration syndrome. In contrast, traditional Korean medicine (TKM) defines CHH as a disease entity in itself which is a key factor for the final diagnosis of cold syndrome pattern. According to one Japanese survey, approximately 60% of the Japanese population suffer from cold syndrome, especially extremity coldness [18]. Facing health care issues, the Japanese government approved insurance coverage of *Kampo* treatment for CHH [19]. However, even though there have been increasing numbers of people experiencing CHH in Korea, policymakers have not yet allowed for broader TKM health insurance coverage or better development of a TKM welfare program.

In designing this trial, we reviewed previous studies by searching various databases (EMBASE, PubMed, CNKI, Oasis). We found several studies on CHH in the traditional medicine field, but its diagnostic criteria and terminology were varied. In addition, most of the studies focused on the occurrence of symptoms upon exposure to cold temperatures.

To determine new diagnostic criteria for CHH in TKM, we organized an Advisory Committee of Experts (ACE) consisting of 10 medical experts, each with more than 10 years of clinical experience, as well as experience treating CHH. The Delphi survey method was used for making accurate decisions. As a result, the collated determination of the ACE was that most Korean women with CHH complain of coldness in the hands at room temperature as well as from cold temperature exposure [1]. Thus, the ACE considered expanding the range of diagnostic criteria to include patients with symptom occurrence both at room temperature and at cold temperatures. Thus, it will be significant to perform a clinical trial using a broader perspective of CHH in TKM. It will also help to define the characteristics of CHH in the Korean population.

Although a few previous studies used infrared thermography to measure the skin temperature with scientific accuracy, this may not reflect the severity of patients’ actual self-report of discomfort due to the limitation of objective measurement. In this exploratory trial, we instead decided to use a VAS score as the primary outcome measure for the severity of CHH changes between baseline (visit 2) and after treatment (visit 5).

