### Trial status

Recruitment is ongoing from December 2015.

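### On its plain reading the liver exclusion needs both AST and ALT above 100 IU/L, so a marked rise in one enzyme alone is left to investigator discretion

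*Protocol article*

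**What the plan says.** In the protocol article, the Exclusion criteria bar women with a moderate degree of liver dysfunction, defined in a bracket as "each of AST and ALT greater than 100 IU/L". A separate branch of the same criterion covers the kidney through creatinine. No other criterion gives a limit for AST or for ALT alone.

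The last exclusion is a general one, for those "judged to be inappropriate for the clinical study by the researchers such as refusal to comply, forgetting visits, lack of comprehension, etc".

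After entry, "participants will take 9 g of DSGOST or placebo drug per day, for 6 weeks" (Interventions). Under Safety assessment, "liver function tests (ALT, AST, and γ-GT), will be conducted at visits 2 and 5". The Discussion identifies visit 2 as baseline and visit 5 as the visit after treatment. Under Adverse event reporting, "All participants will be required to report any adverse events (AE) that occur during the trial at every visit".

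**The concern.** A condition that each of two values exceeds a limit is met only when both exceed it. On that reading, the criterion sets no ceiling on one enzyme while the other is at 100 IU/L or below. A woman with one markedly raised enzyme could be randomised to 6 weeks of daily dosing without breaching any written liver limit.

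Two things are at stake. The first is the safety of that woman: the text lists liver tests only at baseline and after treatment, so the entry threshold is the main written liver safeguard before dosing. The second is consistency: six hospitals apply the sentence, and two careful investigators could reach opposite decisions on the same laboratory report. Bias in the VAS comparison is not at stake, because eligibility is decided before randomisation and applies to both arms alike.

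**Working it through.** The plan gives no figure to reproduce here. The check compares two readings of the criterion and then bounds how many women could be affected.

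**1. The two readings**

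- Plain reading: exclude if AST > 100 and ALT > 100.
- Per-test reading: exclude if AST > 100 or ALT > 100.

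| Illustrative values (IU/L) | Plain reading | Per-test reading |
|---|---|---|
| ALT 300, AST 95 | not excluded | excluded |
| ALT 150, AST 100 | not excluded | excluded |
| ALT 300, AST 101 | excluded | excluded |

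The readings agree when both values are above 100 or both are at or below it. They differ only when exactly one is above.

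**2. What the neighbouring criteria suggest**

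- Blood pressure: systolic above 180 mmHg or diastolic above 100 mmHg. Where either value is enough, this criterion says so. That favours taking the liver wording at face value.
- Haematology: haemoglobin below 7 g/dL, haematocrit below 26% and white cells above 11,000/mm³ stand in one bracket with no connective. Read jointly, the list would require severe anaemia together with a raised white count, which makes little sense. It has to be read test by test, and that favours the per-test reading of the liver bracket.

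The two comparisons point in opposite directions, and neither decides the matter.

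**3. How many women could be affected**

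Inputs: 66 women randomised 1:1, so 33 per arm (Trial design; Randomization). The article does not give the proportion p of otherwise eligible women with exactly one enzyme above 100, so p is assumed over a range.

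Expected number = n × p. Chance of at least one = 1 − (1 − p)^n.

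| Assumed p | Expected of 66 | At least one of 66 | Expected of 33 on DSGOST | At least one of 33 |
|---|---|---|---|---|
| 0.1% | 0.07 | 6% | 0.03 | 3% |
| 0.5% | 0.33 | 28% | 0.17 | 15% |
| 1% | 0.66 | 48% | 0.33 | 28% |

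For example, at p = 0.5%: 66 × 0.005 = 0.33 and 1 − 0.995^66 = 0.28.

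For each assumed p these are upper bounds. They suppose that every site uses the plain reading and that no investigator uses the discretionary exclusion.

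**4. Time between the listed liver tests**

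The treatment period between visits 2 and 5 is 6 × 7 = 42 days.

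**The case against.** The strongest reply is that the criterion was probably meant test by test. The wording can be taken as assigning one cut-off to each enzyme, and the haematology bracket in the same list has to be read that way. The article is also a condensed text with loose English in places, and the full protocol (version 1.5) that the sites work from is not shown. This stands in part. The per-test reading is credible, and the fault may be one of wording rather than of intent. But the article does not choose between the readings, and a numerical safety limit should not depend on guessing what was meant.

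A second reply is that a physician who sees an ALT of 300 can use the general exclusion. That is true, and its examples are not exhaustive. But it is discretionary, its examples concern compliance and comprehension, and it names no laboratory value. It may catch a case, but it does not make the sites act alike.

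A third reply concerns monitoring. Clinic visits take place every 2 weeks, vital signs are taken at each, and adverse events are recorded by the site investigator and assessed for causality. The schedule figure is not available, so whether eligibility bloods are drawn separately from visit 2 cannot be checked. These points soften the concern, although none of these checks is a liver test during treatment.

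A reader might go further and infer that the trial knowingly admits women with marked single-enzyme rises, that such women have been enrolled, or that DSGOST would harm them. The document supports none of this. It reports no laboratory values and states no hepatic hazard of DSGOST, and half of the women receive placebo.

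**Conclusion.** The point holds as a fault of wording in a safety threshold. On its plain reading the criterion requires both enzymes above 100 IU/L. The per-test reading is possible and may be intended, nothing in the article settles it, and on the plain reading only discretion would exclude a woman with one markedly raised enzyme.

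It is a minor point. With an isolated rise in 0.1% to 1% of otherwise eligible women, the number affected is most likely none or one. That range is an assumption with no source in the document. The finding also rests on the article reflecting the wording that the sites use.

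**What to change.** Replace the bracket with *AST or ALT greater than 100 IU/L*, and tell all six sites that one value above the limit is enough to exclude. If the full protocol already says this, a note to the sites that confirms the per-test rule is enough.

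No new test is needed, because both enzymes must already be known to apply the criterion. The trial was "approved by the Institutional Review Board (IRB) of six different hospitals" and "Recruitment is ongoing from December 2015", so the change is an amendment at all six boards, made while the trial is enrolling. It may also cause a few more screen failures. Given the small number likely to be affected, a look-back through women already enrolled is not a necessary part of this change.
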